### ***Ethical implications***

Approval to conduct the study will be sought from the Human Research Ethics Committee of Curtin University and the Department of Health (WA).

### ***Staffing***

One project officer will be appointed at level 4.1 (Curtin General Staff salary level) at 0.2 FTE for 6 months to coordinate the study and manage the data collection, data entry and data storage processes. Data analysis and report writing will be undertaken by Honours students in Pharmacy and/or Physiotherapy degrees at Curtin University. Overall management of the study will be undertaken by a member of the project team (yet to be confirmed).

### ***Feasibility***

Using a partnership arrangement between Health Networks, Curtin University, Musculoskeletal Health Network and the Pharmaceutical Society of Australia, completion of data collection is feasible within 6 months with a budget of \$14,300. It is envisaged that recruitment of participants from 20 pharmacies for each arm of the study will be possible within 4 week blocks; ie 12 participants per pharmacy per 4 week block (3 customers per week). Providing a modest remuneration to each pharmacy will also assist with recruitment.

### ***Budget***

|                                                            |         |
|------------------------------------------------------------|---------|
| Photocopying and postage (\$5 per person)                  | \$1,500 |
| Design and printing of advertising posters                 | \$1,000 |
| Design and printing of teleform sheets for data collection | \$1,000 |
| Design and printing of 500 pamphlets                       | \$500   |
| Training of pharmacists (evening forum)                    | \$500   |
| Project officer (0.2 FTE 6 months, level 4.1 with oncost)  | \$6,200 |
| Remuneration to pharmacies (\$10 per recruit)              | \$3,600 |

**Total**

**\$14,300**

***Appendix 1: Sample size estimates***

BBQ: assuming a mean change of 1.9 points (based on population response in Victoria from Buchbinder et al 2001), STDEV 5.0 (based on WA survey) and 80% power and alpha 0.05, sample of 110 per group needed (N=330).

FABQ-phys: assuming a mean change of 1.5 points (based on population response in Victoria from Buchbinder et al 2001), STDEV 5.0 (based on WA survey) and 80% power and alpha 0.05, sample of 176 per group needed (N=528).

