## ***Design***

A randomized, controlled trial, consisting of 3 study arms (A, B and C), will be undertaken in partnership with 20 community pharmacies in the Perth metropolitan area. A convenience sample of pharmacies will be selected through the PSA-WA. Participating pharmacies will cover major zones of the Perth metropolitan area to represent a range of socioeconomic levels. Ten pharmacies will be involved in both the 'control' (A) and 'pamphlet only' (B) arms while a separate ten pharmacies will be involved in the 'pamphlet with education' (C) arm only. Pharmacies will be allocated to study groups randomly. Each pharmacist who participates in the workshop, will receive training from the evaluation team according to their allocated study arm and remuneration for recruitment.

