## ***Participants***

Pharmacists and/or pharmacy staff will identify individuals who present to the pharmacy to purchase pain-relieving medications for LBP by:

- i) asking customers about the reason for their medication purchase or GP medicine prescription;
- ii) answering questions from customers about medication options for LBP or;
- iii) customers approaching pharmacy staff about the study in response to posters placed in the pharmacy which advertise the study.

Any pharmacy customer aged 18-70 years who is currently experiencing low back pain and has adequate understanding of written and spoken English is eligible to participate. There are no exclusion criteria for this study. Each pharmacy will recruit 12 consecutive customers who meet the inclusion criteria for each study arm. The total sample size will therefore be N=360. Customers who are interested in participating will be asked to complete a consent form and a baseline questionnaire. The completed form and questionnaire will be sent by the pharmacy to Curtin University in a reply paid envelope.

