### ***Outcome measures***

Data will be collected at baseline (T0) and then at 2 weeks (T1), and 8 weeks (T2) after the intervention. Table 1 shows which outcomes measures will be measured at particular time points. Beliefs about back pain will be collected using the Back Pain Beliefs Questionnaire and fear avoidance behaviours will be collected using the Fear Avoidance Beliefs Questionnaire. Pain intensity and disability will be measured using an 11 point numeric rating scale (NRS). Demographic (age, gender, highest level of education) and pain history characteristics (duration of symptoms) will be measured at baseline only while an 11 point NRS for Global Perceived Impression of Usefulness will be used at time points subsequent to baseline to measure the usefulness of the pamphlet.

**Table 1:** Outcome measures assessed by time point.

| Instrument | T0 | T1 | T2 |
|-------------------|-----------|-----------|-----------|
| Demographics      | ✓         |           |           |
| Pain history      | ✓         |           |           |
| BPBQ              | ✓         | ✓         | ✓         |
| FABQ              | ✓         | ✓         | ✓         |
| Pain intensity    | ✓         | ✓         | ✓         |
| GPIU              |           | ✓         | ✓         |
| Disability        | ✓         | ✓         | ✓         |

Participants will be asked to provide informed consent at baseline, including their contact details and date of birth. All data will be collected using a 2 page, teleform paper questionnaire which will be de-identified but linked to person details using a unique study identifier. Data at T0 will be collected onsite at the pharmacy while follow-up questionnaires (T1, T2) will be posted to participants with a reply-paid envelope. All data will be returned to Curtin University for secure storage and analysis. Participants who do not return follow-up questionnaires will be contacted by a project officer and reminded to do so.

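### The 80% power for the beliefs score assumes independent customers and full postal return, so it is unsupported for comparisons with arm C unless baseline correlation is high and 5.0 is a single-score SD

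*Supplement*

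**What the plan says.** Appendix 1 gives the basis for the beliefs score: "BBQ: assuming a mean change of 1.9 points", with an SD of 5.0 taken from a WA survey, and then "80% power and alpha 0.05, sample of 110 per group needed (N=330". It does not say whether 5.0 is the SD of a score or of a change. It gives no ICC, design effect or expected return rate, and neither do the Participants and Analysis sections.

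The Design section says "Pharmacies will be allocated to study groups randomly". Ten pharmacies supply arms A and B, and "a separate ten pharmacies will be involved in the 'pamphlet with education' (C) arm only". Under Participants, "Each pharmacy will recruit 12 consecutive customers who meet the inclusion criteria for each study arm", and "The total sample size will therefore be N=360", which is 120 per arm.

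Under Outcome measures, baseline is completed in the pharmacy, whereas "follow-up questionnaires (T1, T2) will be posted to participants with a reply-paid envelope". A project officer reminds people who do not reply. The Analysis section plans a 3x3 repeated-measures ANOVA with group, time and their interaction, and names no pharmacy term.

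**The concern.** The sample size formula treats each customer as an independent observation who supplies an outcome. Neither condition is secured here. Arm C shares no pharmacy with A or B, so any difference between pharmacies enters the C comparisons directly. Such differences are plausible: pharmacies are chosen to span socioeconomic levels, and the arm C education is given by each pharmacy's own pharmacist. The outcomes at 2 and 8 weeks depend on posted forms.

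Two of the three pairwise comparisons involve C, including C versus B, which is the secondary aim. The beliefs score is also the only outcome for which Appendix 1 supports the planned size, since its own figure for the physical-activity fear-avoidance score is 176 per group against 120 planned. If the 80% is carried over to C versus B, a null result could be read as showing that pharmacist reinforcement adds nothing, when the trial may have had a limited chance of detecting the assumed effect.

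**Working it through.** **Inputs from the documents.** Difference 1.9, SD 5.0, alpha 0.05, power 80%, 110 per group (Appendix 1); 12 customers per pharmacy per arm and N=360 (Participants); ten pharmacies for A and B and ten others for C (Design).

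**Inputs assumed, because the documents give none.** ICC 0 to 0.05; loss by follow-up 0 to 30%; baseline-to-follow-up correlation r 0.5 to 0.7.

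**1. Reproducing 110.** For two independent means, two-sided 5%, the normal approximation gives n = 2 × (5.0 × (1.960 + 0.842) / 1.9)² = 108.7, so 109. The exact t-test gives 79.8% power at 109 and 80.1% at 110. A one-sided test would need 86. The stated 110 is therefore the two-sided t-test answer, with no clustering and no loss.

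**2. The margin.** Recruiting 120 against 110 leaves 10 spare: 10/120 = 8.3% loss (9.2% if measured against 109). If the margin is spent on clustering instead, 1 + 11 × ICC = 120/109 gives ICC = 0.009 (0.008 against 110). It covers one or the other, not both.

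**3. A versus B.** Both arms come from the same ten pharmacies, so a shared pharmacy effect largely cancels and only loss is applied. Individual-level t-test: 83.4% with no loss, 77% at 15%, 74.5% at 20%, 69% at 30%.

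**4. C versus A or B.** With m forms returned per pharmacy per arm, n = 10m and DE = 1 + (m − 1) × ICC:

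SE = 5.0 × √(2 × DE / n); noncentrality = 1.9 / SE; t with 10 + 10 − 2 = 18 df (critical value 2.101).

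Example, ICC 0.02 and 20% loss: m = 9.6, n = 96, DE = 1 + 8.6 × 0.02 = 1.172, SE = 5.0 × √(2 × 1.172 / 96) = 0.781, noncentrality 2.43, power 63%.

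| ICC | Full return (m = 12) | 20% loss (m = 9.6) |
|---|---|---|
| 0 | 79.5% | 70% |
| 0.01 | 75% | 67% |
| 0.02 | 71% | 63% |
| 0.05 | 61% | 55% |

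A normal approximation without the 18 df penalty is kinder: 71.4%, 68.2% and 59.5% at ICC 0.01, 0.02 and 0.05 with 20% loss.

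**5. Offset from baseline, if 5.0 is a single-score SD.** A change-score contrast multiplies the variance by 2(1 − r): 1.0, 0.8 and 0.6 at r = 0.5, 0.6 and 0.7. A baseline-adjusted model multiplies it by 1 − r²: 0.75, 0.64 and 0.51. Power for comparisons with C (18 df, same ICC kept for simplicity):

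| Scenario | No baseline | Change, r 0.6 | Change, r 0.7 | Adjusted, r 0.6 | Adjusted, r 0.7 |
|---|---|---|---|---|---|
| ICC 0.01, full return | 75% | 84% | 93% | 91% | 96% |
| ICC 0.02, 20% loss | 63% | 73% | 84% | 82% | 90% |
| ICC 0.05, 20% loss | 55% | 64% | 77% | 74% | 83% |

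At r = 0.5 the change contrast gains nothing, and below that it loses. If 5.0 is already a change SD, the change contrast brings no gain at all.

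**The case against.** The best reply is that baseline is already in the plan. The beliefs score is collected at all three time points and the group-by-time interaction is tested, so an unadjusted comparison at one time is not quite the planned test. If 5.0 is a single-score SD and r is about 0.6 to 0.7, several of the scenarios above return to 80% or more. That stands, and it is why the shortfall must be stated conditionally.

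Second, the only shortfall that needs no assumed ICC or loss is half a percentage point, and it comes from an 18-df cluster-level test that the plan does not name. With individual-level df and the same inputs, 120 per arm gives 83.4%. This also stands as a matter of size. However, 18 df is what a contrast between ten and ten allocated pharmacies supports, and the 83.4% again assumes that customers are independent.

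Third, non-responders are reminded, the 10 spare recruits per arm do act as an unlabelled margin, and no figure in the documents points to 15% to 30% loss. The loss range is therefore an assumption.

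Fourth, Appendix 1 does not name C versus B as having 80% power, and it openly reports a requirement for fear avoidance that exceeds the planned size. It does, however, multiply 110 by three groups without distinguishing the comparisons, so a reader will apply it to all of them.

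**Conclusion.** The arithmetic behind 110 is right; what is missing is the fit to the design. The 80% holds for independent customers with full return. For A versus B it survives loss up to about 8%. For comparisons with C, on 1.9 and 5.0 alone, power is at most 79.5%, and it is 75% to 61% (full return) or 67% to 55% (20% loss) under assumed ICCs of 0.01 to 0.05. The 80% is therefore unsupported for those comparisons unless 5.0 is a single-score SD and baseline correlation is high.

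A reader might infer that Appendix 1 contains a calculation error, or that the trial is definitely underpowered for arm C. The documents support neither. The first is ruled out because 110 reproduces. The second would need an ICC, a return rate, a correlation and the meaning of 5.0, none of which is given. The omission is certain; the size of the shortfall is not.

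**What to change.** Keep N=360 and rewrite the beliefs-score part of Appendix 1:

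- Give power separately for A versus B (within pharmacy) and for comparisons with C (ten versus ten pharmacies, 18 df).
- State a range for the ICC and for the postal return rate, with sources where available, and tabulate power over both.
- Say whether 5.0 is the SD of a score or of a change.
- Show the offset from baseline: factor 2(1 − r) for the change or interaction contrast already planned, or 1 − r² if a baseline-adjusted model is adopted, over a stated range of r.

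The cost is recalculation and a few lines of text, with no added participants. The downside is a less favourable stated power for comparisons with C, including the secondary aim.

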## ***Aim***

The aim of this project is to undertake an evaluation of the LBP pamphlet within a primary care context. The SPIWG will partner with Curtin University and the Pharmaceutical Society of Australia (WA) (PSA-WA) for the evaluation. The project will determine whether providing the pamphlet to individuals who visit a community pharmacy to purchase pain-relieving medications for LBP is effective in improving beliefs about LBP and minimising fear avoidance behaviours related to LBP, compared to not providing the pamphlet. A secondary aim is to determine whether providing the pamphlet with the pharmacist reiterating the key messages to the consumer is more effective than providing the pamphlet alone.

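### Appendix 1 requires 528 participants for fear avoidance, which the primary aim names without ranking; the plan enrols 360 and does not acknowledge the shortfall

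*Supplement*

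**What the plan says.** The Aim section sets out to learn whether giving the pamphlet "is effective in improving beliefs about LBP and minimising fear avoidance behaviours related to LBP, compared to not providing the pamphlet". The two outcomes are joined without a ranking. The secondary aim in that section compares two ways of delivering the pamphlet; it does not place one outcome below the other.

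Under Outcome measures, "fear avoidance behaviours will be collected using the Fear Avoidance Beliefs Questionnaire", next to the back beliefs questionnaire, again unranked.

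Appendix 1 gives one sample size per outcome:

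- Back beliefs: change 1.9, SD 5.0, 80% power, alpha 0.05; 110 per group, N=330.
- Fear avoidance: "FABQ-phys: assuming a mean change of 1.5 points", with SD 5.0, 80% power and alpha 0.05; "sample of 176 per group needed (N=528").

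The Participants section sets 12 customers per pharmacy per arm and concludes: "The total sample size will therefore be N=360". Interventions confirms 120 in each of arms A, B and C.

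**The concern.** The plan calculates a requirement for an outcome in its primary aim and then recruits about two thirds of it (360/528 = 68%). The text shown does not say that 360 was chosen for back beliefs, that fear avoidance ranks lower, or that power for it is reduced.

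At stake is how a null FABQ result would be read. The only power figure given for this outcome is the 80% behind the 528. A reader who saw that figure and a null result might conclude that the pamphlet does not change fear avoidance. In fact, even if the assumed 1.5-point effect were real, the simple comparison would miss it more than one time in three with complete follow-up.

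**Working it through.** **Inputs.** From Appendix 1: differences 1.9 (back beliefs) and 1.5 (FABQ-phys), SD 5.0, power 80%, alpha 0.05. From Participants and Interventions: 10 pharmacies × 12 customers = 120 per arm; 3 × 120 = 360. No allowance for loss to follow-up and no intracluster correlation (ICC) is stated.

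**1. Reproducing the plan's figures.** For two independent means, two-sided, n per group ≈ 2·SD²·(1.960 + 0.842)²/δ².

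- δ = 1.9: 2 × 25 × 7.849/3.61 = 108.7; with the t-distribution 109.7, rounded up to 110. Matches.
- δ = 1.5: 2 × 25 × 7.849/2.25 = 174.4; with the t-distribution 175.4, rounded up to 176. Matches; 3 × 176 = 528.

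Appendix 1 does not state sidedness. A one-sided test would give 138 for FABQ-phys, so the plan's figure is two-sided. Its arithmetic is correct.

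**2. Shortfall.** 176 − 120 = 56 per group; 528 − 360 = 168 in total. For back beliefs, 360 exceeds 330 by 30.

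**3. Power at the planned size.** The standard error of a difference is 5.0 × √(2/120) = 0.645.

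- FABQ-phys: 1.5/0.645 = 2.32, giving 63.9% power (t-distribution) or 64.2% (normal approximation).
- Back beliefs, for comparison: 83.4% (t) or 83.7% (normal).
- Difference detectable with 80% power: 2.80 × 0.645 = 1.81 points; 1.82 with the t-distribution.

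**4. Sensitivity of the FABQ-phys figure** (t-distribution; loss and ICC are assumptions, since the plan gives neither).

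| Assumption | Effective n per group | Power for 1.5 points |
|---|---|---|
| None | 120 | 64% |
| 10% loss | 108 | 59% |
| 20% loss | 96 | 54% |
| 30% loss | 84 | 49% |
| ICC 0.01, design effect 1 + 11 × 0.01 = 1.11 | 108.1 | 59% |
| ICC 0.02, design effect 1.22 | 98.4 | 55% |
| ICC 0.05, design effect 1.55 | 77.4 | 46% |

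The ICC rows treat the two arms as separate sets of pharmacies. That fits comparisons of arm C (pharmacies 11–20) with A or B (pharmacies 1–10). It does not describe A against B, which share pharmacies.

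**The case against.** **The plan never says that 360 gives 80% power for FABQ.** This stands. A reader might infer that the plan promises 80% power and fails to deliver it. The documents do not support that: in Appendix 1 the 80% is an input to the 528, and the Participants section derives 360 from recruitment per pharmacy with no power claim. What remains is a stated requirement that the design does not meet and does not discuss.

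**The 64% is not the power of the planned analysis.** This also stands. The Analysis section plans a 3×3 ANOVA with one repeated measure, whereas Appendix 1 and the check above compare two groups once. Use of the baseline could recover power. If 5.0 is a cross-sectional SD, a baseline-adjusted comparison at 120 per arm has about 76% power at an assumed baseline-to-follow-up correlation of 0.5 and about 82% at 0.6. A contrast of mean follow-up minus baseline, with equal correlations between visits and the same effect at both follow-ups, has about 62%, 76% or 93% at 0.3, 0.5 or 0.7. But the plan gives no such correlation, specifies no baseline adjustment, and does not say whether 5.0 is a cross-sectional or a change SD. Loss works the other way: at 0.6 with 20% lost, the adjusted figure is 73%. Adequate power is therefore possible but not shown.

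**Two unranked outcomes allow either to be claimed at 5%.** A reader might infer this, but the text does not establish it. The aim joins the outcomes with *and*; if both had to improve, there would be no such inflation. The plan states no decision rule either way, so no multiplicity charge is made here.

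**FABQ-phys is only a subscale.** True: the aim and the outcome section refer to fear avoidance and the FABQ generally, and the questionnaire includes work items. FABQ-phys is nevertheless the only fear-avoidance estimate offered.

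**360 was evidently chosen for back beliefs.** Plausible, since 360 exceeds 330 and beliefs are listed first throughout. The plan does not say so.

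**Conclusion.** The point holds as an unacknowledged shortfall. By the plan's own estimate, fear avoidance needs 176 per group and will have 120. On Appendix 1's inputs (difference 1.5, SD 5.0, two-sided alpha 0.05), a simple two-group comparison then has about 64% power, and about 1.8 points rather than 1.5 is detectable with 80% power. These figures assume complete follow-up and no clustering, and concern FABQ-phys only. For comparisons with arm C, assumed ICCs of 0.01 to 0.05 bring power to about 59% to 46%.

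The sample size arithmetic is right, and back beliefs are covered on the plan's assumptions before loss and clustering. What is missing is a statement of which outcome N=360 serves and what it offers the other.

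**What to change.** Without adding participants:

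1. State in Participants or Appendix 1 that N=360 is sized on the back beliefs score as the primary outcome, and make FABQ-phys secondary in the Aim and Outcome measures sections.
2. Replace the FABQ line in Appendix 1 with wording such as: *At the planned 120 per group, a simple two-group comparison of FABQ-phys (two-sided alpha 0.05, SD 5.0) has about 64% power for a difference of 1.5 points, and about 1.8 points is detectable with 80% power. These figures are before loss to follow-up and before clustering by pharmacy, which lowers power further for comparisons with arm C (for example, to about 59% to 46% at assumed ICCs of 0.01 to 0.05).* The caveats must stay: the 64% alone would be too favourable for the comparisons with arm C.

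The cost is protocol wording and a less favourable stated figure. The ranking should be settled before outcome data are seen.

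If the sponsor wants fear avoidance to keep equal standing, the alternative is to recruit the plan's own 528. At the Budget's unit costs ($10 remuneration and $5 photocopying and postage per person), 168 more participants add 168 × $15 = $2,520 to the $14,300, before any extra staff time. Even 528 makes no allowance for loss or clustering.

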# LOW BACK PAIN IN PRIMARY CARE QUESTIONNAIRE

## Time 0 (baseline)

### COMPLETION INSTRUCTIONS

Please shade the circles completely ● Please write clearly in the boxes or free text areas

1 2 3 ABCDE

Please read and answer questions carefully. Do not take long to answer the questions, however it is important that you answer every question. There is always a response for your particular situation.


24917

[figure not shown]

# LOW BACK PAIN IN PRIMARY CARE QUESTIONNAIRE

## Time 1 (at 2 weeks post initial questionnaire)

### COMPLETION INSTRUCTIONS

Please shade the circles completely ● Please write clearly in the boxes or free text areas

1

2

3

ABCDE

Please read and answer questions carefully. Do not take long to answer the questions, however it is important that you answer every question. There is always a response for your particular situation.

### SECTION A: LOW BACK PAIN

- A1. Considering your low back pain over the last 24 hours, please rate the average severity of low back pain you have experienced on the scale below where 0 means 'no pain' and 10 means 'worst pain imaginable'.

| No pain               |                       |                       |                       |                       |                       |                       |                       |                       |                       |                       | Worst pain            |
|-----------------------|-----------------------|-----------------------|-----------------------|-----------------------|-----------------------|-----------------------|-----------------------|-----------------------|-----------------------|-----------------------|-----------------------|
| 0                     | 1                     | 2                     | 3                     | 4                     | 5                     | 6                     | 7                     | 8                     | 9                     | 10                    |                       |
|  |  |  |  |  |  |  |  |  |  |  |  |

- A2. Considering your low back pain over the last 24 hours, please rate how this has affected your normal activities of daily living on the scale below, where 0 means 'not affected at all' and 10 means 'unable to perform any activities of daily living'.

| Not affected at all   |                       |                       |                       |                       |                       |                       |                       |                       |                       |                       | Unable to perform any activities of daily living |
|-----------------------|-----------------------|-----------------------|-----------------------|-----------------------|-----------------------|-----------------------|-----------------------|-----------------------|-----------------------|-----------------------|--------------------------------------------------|
| 0                     | 1                     | 2                     | 3                     | 4                     | 5                     | 6                     | 7                     | 8                     | 9                     | 10                    |                                                  |
|  |  |  |  |  |  |  |  |  |  |  |                             |

- A3. For each statement below please indicate how much physical activities (such as bending, lifting, walking or driving) and work activities affect or would affect your back pain. (Please shade one circle for each question)

|                                                                          | Completely disagree   | Moderately disagree   | Slightly disagree     | Unsure                | Slightly agree        | Moderately agree      | Completely agree      |
|--------------------------------------------------------------------------|-----------------------|-----------------------|-----------------------|-----------------------|-----------------------|-----------------------|-----------------------|
|                                                                          | 0                     | 1                     | 2                     | 3                     | 4                     | 5                     | 6                     |
| a) My pain was caused by physical activity.                              |  |  |  |  |  |  |  |
| b) Physical activity makes my pain worse.                                |  |  |  |  |  |  |  |
| c) Physical activity might harm my back.                                 |  |  |  |  |  |  |  |
| d) I should not do physical activities which (might) make my pain worse. |  |  |  |  |  |  |  |
| e) I cannot do physical activities which (might) make my pain worse.     |  |  |  |  |  |  |  |
| f) My pain was caused by my work or by an accident at work.              |  |  |  |  |  |  |  |
| g) My work aggravated my pain.                                           |  |  |  |  |  |  |  |
| h) I have a claim for compensation for my pain.                          |  |  |  |  |  |  |  |
| i) My work is too heavy for me.                                          |  |  |  |  |  |  |  |
| j) My work makes or would make my pain worse.                            |  |  |  |  |  |  |  |
| k) My work might harm my back.                                           |  |  |  |  |  |  |  |

[figure not shown]

[figure not shown]

24917

[figure not shown]

**A3. (continued) For each statement below please indicate how much physical activities (such as bending, lifting, walking or driving) and work activities affect or would affect your back pain.**  
(Please shade one circle for each question)

|                                                                          | Completely disagree
0 | Moderately disagree
1 | Slightly disagree
2 | Unsure
3           | Slightly agree
4   | Moderately agree
5 | Completely agree
6 |
|--------------------------------------------------------------------------|--------------------------|--------------------------|------------------------|-----------------------|-----------------------|-----------------------|-----------------------|
| l) I should not do my normal work with my present pain.                  |     |     |   |  |  |  |  |
| m) I cannot do my normal work with my present pain.                      |     |     |   |  |  |  |  |
| n) I cannot do my normal work until my pain is treated.                  |     |     |   |  |  |  |  |
| o) I do not think that I will be back to my normal work within 3 months. |     |     |   |  |  |  |  |
| p) I do not think that I will ever be able to go back to my normal work. |     |     |   |  |  |  |  |

**A4. We are interested in what you think about back pain generally. Please indicate your general views about back trouble.**  
(Please answer the statements below by selecting one response to each statement)

|                                                                      | Completely disagree
1 | 2                     | 3                     | 4                     | Completely agree
5 |
|----------------------------------------------------------------------|--------------------------|-----------------------|-----------------------|-----------------------|-----------------------|
| a) There is no real treatment for back trouble.                      |     |  |  |  |  |
| b) Back trouble will eventually stop you from working.               |     |  |  |  |  |
| c) Back trouble means periods of pain for the rest of one's life.    |     |  |  |  |  |
| d) Doctors cannot do anything for back trouble.                      |     |  |  |  |  |
| e) A bad back should be exercised.                                   |     |  |  |  |  |
| f) Back trouble makes everything in life worse.                      |     |  |  |  |  |
| g) Surgery is the most effective way to treat back trouble.   |     |  |  |  |  |
| h) Back trouble may mean you end up in a wheelchair.                 |     |  |  |  |  |
| i) Alternative treatments are the answer to back trouble.            |     |  |  |  |  |
| j) Back trouble means long periods of time off work.                 |     |  |  |  |  |
| k) Medication is the only way of relieving back trouble.      |     |  |  |  |  |
| l) Once you have had back trouble there is always a weakness. |     |  |  |  |  |
| m) Back trouble must be rested.                               |     |  |  |  |  |
| n) Later in life back trouble gets progressively worse.              |     |  |  |  |  |

